### Outcomes

A physician will follow the participants’ blood glucose levels un-blinded, a week before each assessment session. This control will be based on an email report of the daily blood glucose levels 7 days before the training session.

During each of the assessments (visits 3 and 6; see Table 3) a CGM will be installed at 7:00 a.m. and will be maintained until 48 h after the training session ends. During each of these visits the participants will perform the soccer performance evaluation at 5:00 p.m. These training sessions must be separated by 3 weeks, with the idea of reducing a possible “learning effect” associated with repeated workouts. In the 48 h following each training session, participants will be required to measure their blood glucose level eight times (i.e., 2 h after dinner, before going to bed, at 12:00 a.m., at 3:00 a.m., just before breakfast, 2 h after breakfast, just before lunch, 2 h after lunch, and just before dinner). They will also be provided with a form where they will be required to register the appearance and timing of symptoms of hypoglycemia. Blood glucose level will be evaluated using the Accu-Chek® Nano Glucometer (Roche Servicios SA, Costa Rica) 30 min before each assessment session, after each one of the workouts, and before both the basal and 24-h cognitive tests.

**Table 3 Tab3:** Study visits summary table

Assessments and interventions	Pre-screening	Visit 1	Visit 2	Visits 3, 6	Visit 5	Visits 4, 7
Review of eligibility criteria	X					
Demographic data and clinical evaluation		X				
BMI measurement and laboratory evaluation		X				
Theoretical and practical explanation of training exercises			X			
4-Step method and usual care recommendations educational sessions			X		X	
Training sessions with simulated soccer exercises (LIST-P, LSST, LSPT)				X		
Cognitive evaluations				X		X
Efficacy of blinding assessment					X	X
Revision of self-monitoring of blood glucose after exercise session						X
Approximated time	30 min	60 min	90 min	120 min	90 min	60 min

*BMI* body mass index, *LIST-P* Loughborough Intermittent Shuttle Test Prescribed and Self-Paced, *LSST* Loughborough Soccer Shooting Test, *LSPT* Loughborough Soccer Passing Test

After completing the first evaluation, participants will change their interventional arm, and both groups will receive a second educational session (visit 5) from an endocrinologist, who will explain the details of their new dietary and pharmacological interventions. Also in this visit, we will assess the efficacy of blinding by asking participants in which interventional arm they think they are allocated, and how confident they are about their answer.

Furthermore, participants will be seen the day following each assessment visit (visits 4 and 7) during which cognitive testing and self-monitoring of blood glucose will be repeated. In the last visit (visit 7) we will assess the efficacy of blinding again by asking participants in which interventional arm they think they were allocated, and how confident they are about their answer.

All participants will be instructed to replicate and record their diets (MyFitnessPal App®) and maintain their current insulin regimen, without modifying the dose, injection site, or time of injection for 24 h before each experimental trial day (visits 3 and 6). Participants will also be instructed to maintain similar grades of physical activity during the trial, avoiding strenuous exercise during the previous 48 h and 48 h following the simulated soccer drills.

The assessment sessions will occur on two separate days (separated by 3 weeks) and consist of both cognitive and physical activity evaluations. During the physical activity assessments participants’ heart rate (HR) will be traced with a Garmin Vivofit 2 Bundle with HR monitor (Garmin^©^, Kansas, USA).

### Primary outcome

We will compare the percentage of participants with one or more confirmed hypoglycemic episodes (≤60 mg · dL^-1^) in the next 24 h following the assessment session. Other safety-related end points include changes in the mean and variability of 24-h plasma glucose based on CGM. Percentages of participants with hypoglycemic events will be calculated as categorized by the ADA^70^ and will be analyzed during the day (daytime; 6:00 a.m. to 11:59 p.m.), during the night (nocturnal; 12:00 midnight to 05:59 a.m.), and any time of day or night (24 h).

Precisely, hypoglycemic categories will include the following: (1) any hypoglycemia (events whether confirmed by self-measurement or not and whether symptomatic or asymptomatic); (2) documented symptomatic hypoglycemia (symptomatic events with plasma glucose ≤60 mg · dL^-1^); (3) asymptomatic hypoglycemia (events confirmed by plasma glucose ≤60 mg · dL^-1^ but without symptoms); and (4) severe hypoglycemia (events requiring assistance by another person to administer carbohydrate, glucagon, or other therapy). Confirmed or severe hypoglycemia will include documented symptomatic or asymptomatic events together with severe events.

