## Methods

### Research aim

The aim of this research is to assess the safety (evaluated as rate of hypoglycemia) that this 4-step strategy has on patients with T1D after completing a series of simulated soccer tests. As exploratory analysis, we will compare the performance of the skills required to achieve a good score in the selected test. We will also aim to identify an optimal pre-exercise blood glucose level associated with a better performance in simulated soccer tests. Finally, we will evaluate the effect of this 4-step strategy for blood glucose level control in the cognitive performance (indexed by neuropsychological evaluations testing executive functions, attention, working memory, psychomotor speed, and visual-spatial short-term memory) in patients diagnosed with T1D.

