**Fig. 4 Fig4:**

Schematic representation of the order of soccer assessments according to the protocol. *LIST-P* Loughborough Intermittent Shuttle Test Prescribed and Self-Paced, *LSST* Loughborough Soccer Shooting Test, *LSPT* Loughborough Soccer Passing Test

Additionally, as exploratory outcomes we will also assess cognitive functions, given that hypoglycemia has long been thought to influence these functions in people with diabetes mellitus. A field study of school-aged children with T1D has shown that low blood glucose level impairs patients’ sports performance and produces detrimental cognitive effects, as measured by math test performance [8]. In this sense we set forth to evaluate, as a secondary outcome, the effect of the 4-step method on the cognitive performance of the subjects, related also to the frequency of hypoglycemic events and to the performance in soccer indexed by the tests described. We hypothesize that besides showing an adequate safety profile (same or reduced number of hypoglycemic events), the 4-step method will also allow the subjects to achieve a better performance both in soccer and in cognitive testing (see Fig. 5 for a summary of the planned study interventions and assessments).

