### Sample size

We estimated a sample size of 24 participants per group, yielding a total sample size of 48 participants. However, because of the crossover design of this trial we will only need a total of 24 participants, as each of them will participate in both interventional arms. We used the following parameters for the sample size calculation: an alpha value of 0.05, power of 80%, two different intervention groups with a crossover design, and a minimal clinically important difference between the groups compared of 40% in the frequency of hypoglycemic events. Considering also a 15% dropout rate during the clinical trial, we obtained a required sample size of 28 participants for each group.

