### Statistical methods

In order to evaluate glucose control, we will also compare the two groups, using either Student’s paired *t* test or the Wilcoxon-Mann-Whitney test, in terms of CGM parameters that include: 24-h mean glucose levels, SD of 24-h glucose levels, area under the curve for 24-h glucose, mean amplitude of glycemic excursions, number of episodes of hypoglycemia (<60 mg · dL^-1^), time in hypoglycemia (<60 mg · dL^-1^) during a 24-h period, time in hyperglycemia (>180 mg · dL^-1^) during a 24-h period, and range of postprandial glucose increase. The range of glucose increase (from pre-meal to post-prandial peak levels) after breakfast, lunch, and dinner, will also be compared between the interventional groups, using either repeated measures analysis of variance (ANOVA) or the Kruskal-Wallis test, depending on the normality of the data distribution.

We will assess for data from the LIST-P, LSPT, and LSST, and the Stroop, DVT, DBT, and RVIP test scores obtained for each assessment session, for normality of distribution using histogram analysis, the Shapiro-Wilk test and the Kolmogorov-Smirnov test. We will use a logarithmic transformation for the correction of non-normal data and will subsequently test for the differences between groups using Student’s paired *t* test. In order to assess if the order of the intervention modified the performance of individual participants, we will calculate the difference of the scores obtained between the two types of interventions (real intervention minus sham 4-step method) and then we will define an intervention indicator variable that will take the value of 1 if the subject started with the real 4-step method, and 0 if the subject started with the sham 4-step method. We will then fit a linear regression model with the difference calculated as the response variable and the intervention indicator along with other relevant covariates (age, gender, BMI) as the independent variables. Moreover we will test for time effect over the performance of the participants in a time-varying regression model. Additionally, Pearson correlation coefficients will be calculated between each of the scores and the pre-exercise blood glucose level, searching for linear correlation between blood glucose values and the LIST-P, LSPT, LSST, and Stroop test scores.

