In the event that the data do not follow the normal distribution even after the log-transformation, we will conduct non-parametric analyses using the Wilcoxon-Mann-Whitney test and calculate Spearman correlation coefficients for the comparison between the two groups of the performance scores in soccer and cognitive tests, and for the linear correlation analysis, respectively. A *p* value <0.05 will be considered significant for the comparison of the scores.

Additionally, we will conduct exploratory analyses by modeling the performance scores in soccer evaluations adjusted by age, years since T1D diagnosis, HbA1c level, weekly physical activity hours and Stroop test scores using linear multiple regression. A *p* value <0.10 will be considered significant to introduce a variable into the multivariate regression model. The number of hypoglycemic events and the percentage of other adverse effects listed previously will also be compared among groups using Student’s *t* test and the Fisher exact test, respectively. All of the statistical analysis will be done using Stata software (StataCorp LP® 13.1).

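### The primary outcome is the percentage of participants with at least one confirmed hypoglycemic episode, but the statistical methods name no test for it and test the number of events instead

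*Protocol article*

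**What the plan says.** All references are to the protocol article.

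- **Primary outcome:** "We will compare the percentage of participants with one or more confirmed hypoglycemic episodes", with a glucose threshold and a 24 h window after the session. Each participant counts once per period, however many episodes occur.
- **Statistical methods, last paragraph:** "The number of hypoglycemic events and the percentage of other adverse effects listed previously will also be compared among groups". The sentence then names Student's t test and the Fisher exact test, in that order and respectively. The t test therefore belongs to the event count and the Fisher test to the other adverse effects.
- **Statistical methods, first paragraph:** the list of CGM parameters includes "number of episodes of hypoglycemia" and time in hypoglycemia, compared by a paired t test or a Wilcoxon-Mann-Whitney test.
- **Research aim:** the trial is to "assess the safety (evaluated as rate of hypoglycemia").
- **Secondary outcomes, introduction to the cognitive tests:** an adequate safety profile is glossed as "same or reduced number of hypoglycemic events".
- **Sample size:** the difference to detect is "40% in the frequency of hypoglycemic events".

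**The concern.** The article does name tests for hypoglycemia, but none of them addresses the quantity it calls primary. An analyst who followed Statistical methods literally would report hypoglycemia as a t test on event counts, plus CGM counts and durations. The percentage could appear without a test, or with one chosen later.

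The two quantities can part company. A participant with five lows counts once in the percentage and five times in the count, so in a small trial a few people with recurrent lows can dominate the count. If both comparisons are at hand and neither is tied to the primary outcome, the choice between them can be made after the results are seen.

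**Working it through.** **1. Which quantity does each stated test address?**

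| Quantity | Named test |
|---|---|
| Percentage with one or more confirmed episodes in 24 h (primary) | none |
| Number of hypoglycemic events | Student's t test |
| Percentage with other adverse effects | Fisher exact test |
| CGM number of episodes, time in hypoglycemia | paired t or Wilcoxon-Mann-Whitney |

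**2. Which quantity does the sample size fit?** Inputs from Sample size: alpha 0.05 (two-sided assumed), power 80%, difference 40%, and 24 before dropout. The control level is not given, so it is assumed below.

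*As a percentage, 40 points absolute.* With p̄ = (p1 + p2)/2, n per group = [1.96·√(2p̄(1−p̄)) + 0.842·√(p1(1−p1) + p2(1−p2))]² / (p1−p2)². For 70% v 30% this is (1.386 + 0.545)² / 0.16 = 23.3, so 24. Both 65% v 25% and 75% v 35% also give 24. The stated figure is reproduced, and 24 × 1.15 = 27.6 gives the 28 after dropout.

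*Same contrast, paired (McNemar).* n = [1.96·√d + 0.842·√(d − 0.16)]² / 0.16, where d is the discordant proportion. With independent responses d = 0.49 + 0.09 = 0.58 and n = 26. With a within-person correlation of 0.3 between the binary responses, d = 0.427 + 0.027 = 0.454 and n = 20. The stated 24 lies between these.

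*As a 40% relative fall in a mean count* (Poisson, independent periods, control mean m): n = 7.85 × (m + 0.6m) / (0.4m)² = 78.5/m. That is 157, 79, 40 and 27 pairs for m = 0.5, 1, 2 and 3. A count would need a control mean of about 3 episodes or more in 24 h to come near 24.

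**3. Can the two quantities disagree in 24 participants?** Two constructed cases show that they can, in either direction:

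- The same 12 of 24 participants are affected in both periods, with three episodes each under control and one each under treatment (36 v 12 events). The percentages are identical; the paired t test on counts gives p = 0.00008.
- 14 v 4 of 24 participants are affected, with 14 events in each period. There are ten discordant pairs, all in one direction, so exact McNemar p = 2 × 0.5¹⁰ = 0.002. The t test gives p = 1.0.

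**4. How often?** Simulation of 24 pairs, 70% v 30% affected, latent within-person correlation 0.3, 20,000 trials per row. All count distributions are assumptions.

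| Assumed episode counts | Exact McNemar rejects | Paired t on counts rejects | Verdicts differ |
|---|---|---|---|
| Poisson (means 1.20 v 0.36) | 79% | 96% | 18% |
| One episode plus overdispersed extras, mean 1, negative binomial dispersion 1 | 79% | 57% | 29% |
| The same, dispersion 0.5 | 79% | 51% | 34% |

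A second set of runs used Poisson counts with 40% fewer events and independent periods (10,000 trials each). At control means 1, 2 and 3, McNemar rejects in 15%, 16% and 8% of trials and the paired t test in 31%, 56% and 73%. Verdicts differ in 20%, 43% and 66%.

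Disagreement is common under every assumption tried. The ordering of power is not stable: the count test gains under Poisson counts and loses when a few participants have many repeat episodes.

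**The case against.** The strongest reply is that the primary endpoint is fixed once, clearly, under its own heading, and no other section calls a count primary. On that view only the name of a test is missing, and an article may leave that to a fuller document. The event-count sentence sits in a paragraph that opens with exploratory analyses and says the count will also be compared, so it can be read as an addition.

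Much of this stands. A reader might infer that the article holds several rival primary endpoints, or that it abandons the percentage. The text does not support that: the Primary outcome section commits to the comparison. Rate, in Research aim, is an everyday word for the proportion affected, and the phrase before the cognitive tests is a parenthetical gloss. Frequency of events, in Sample size, is imprecise, but the figure it produces is that of a percentage.

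A reader might also infer that the t test on counts is the weaker choice. That holds only under overdispersed episodes and reverses under Poisson counts, and the article gives no episode distribution.

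The reply does not dispose of the central gap. The article goes beyond silence about a test: it states its hypoglycemia tests and attaches all of them to other quantities, and it restricts its one test of percentages to other adverse effects. An analysis plan built on that section would carry the mismatch forward.

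**Conclusion.** The concern holds in a limited form. The primary percentage has no assigned test, and the hypoglycemia tests that are stated address event counts and CGM durations. At 70% v 30% affected, the count and the percentage gave different verdicts in about 18% to 34% of simulated trials of 24 participants. These figures rest on assumed control percentages, within-person correlation and episode counts. They show that the choice matters, and they do not forecast this trial or show which test is more powerful.

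The sample size does not conflict with the primary outcome: 24 follows from a 40-point absolute difference in percentages. That is agreement with the planning formula and not spare power. In simulation, exact McNemar with 24 pairs reached 79% at latent correlation 0.3 and 70% with independent responses.

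**What to change.** - **Statistical methods:** state that the primary comparison is the within-participant difference in the percentage with one or more confirmed episodes in 24 h, as defined under Primary outcome, tested with a paired binary method such as exact McNemar. Label the number of events as secondary, analysed within participant with a method suited to counts.
- **Research aim, and the safety hypothesis before the cognitive tests:** replace rate and number of events with the Primary outcome wording.
- **Sample size:** say that the 40% is an absolute difference in the percentage of participants affected, if that is what was meant, and give the two percentages assumed.

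The cost is wording in four places and one extra line of analysis. No new data are needed and the sample size stays as it is. The change should be made before anyone sees outcome data by arm.

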### Secondary outcomes

The secondary outcomes will be comparisons of physical and technical performance in soccer training sessions between groups through the tests as subsequently described.

#### Loughborough Intermittent Shuttle Test – Prescribed and Self-Paced (LIST-P)

A modified and validated LIST protocol will be used as an equivalent to the intermittent physical activity that is performed during a soccer match. The LIST-P [17] requires participants to run back and forth between two lines 20 m apart. Each block of exercises consists of ~11 repeated cycles of walking, running (at a speed equivalent to 95% VO_2_ max), jogging (at a speed equivalent to 55%) and sprinting (defined as running to the maximum effort according to maximum VO_2_ max). Further, each cycle includes three repeated shuttles of walking, one 15-m sprint, three repeated shuttles of running and three repeated shuttles of jogging (Fig. 1). Audio signals will help to dictate the speeds at which participants will complete each shuttle.

**Fig. 1 Fig1:**
[figure not shown]
Schematic representation of the Loughborough Intermittent Shuttle Test - Prescribed and Self-paced (*LIST-P*). Modified from Ali et al. [17]

The LIST-P will be modified to complete 45 min of the test. This reduction in test duration will be established in order to adjust the time of all evaluations to approximately 60 min. Consequently, this 1-h training session will have some similarity with previous clinical trials of continuous physical activity and T1D in terms of exercise duration, with the possibility of comparing the rate of hypoglycemic episodes and blood glucose control in participants. Therefore, the first two blocks of exercises (Blocks 1 and 2 in Fig. 1) will be performed at a prescribed-pace while the third and fourth blocks will be “self-paced” (Block 3 in Fig. 1).

Prescribed pace is established according to the VO_2_max reported during initial evaluation of the subject, when he or she was included in the clinical trial. On block 1 of LIST-P the prescribed pace includes repetitions of running at 95% VO_2_ max and 55% VO_2_ max (Fig. 1), whereas self-paced running will be defined and tailored specifically according to the subject’s preference. The auto-imposed pace will try to simulate conditions experienced during real gameplay, where subjects will run faster or slower depending on their physical capacity.

Prior to the beginning of the self-paced section, one of the investigators will ask participants to replicate the intensity and pattern of exercises done during the prescribed-pace period over the self-paced blocks of exercises. Evaluators will give no other verbal instructions during the self-paced blocks. The evaluators will record the duration of time spent on each activity mode (e.g., walking, running, jogging) for the self-paced cycle and for the total distance covered in the 15-min block.

Participants will consume 5 mL · kg^-1^ of a sugar-free sport drink (Powerade Zero ®, Coca-Cola Company) before starting exercise, and then 3 mL · kg^-1^ body mass of the same beverage every 15 min during the LIST-P protocol. Additionally, investigators will record body mass before and after each training session. Immediately after finishing each of the blocks from the LIST-P, participants will undergo psychometric testing using the perceived exertion scale (RPE) [18], the felt arousal scale (FAS) [19] and the feeling scale (FS) [20].

The participants will complete three 15-min blocks of the LIST-P punctuated by 4-min resting periods. After having completed the last block of LIST-P, participants will have 5 min of recovery time, and another finger-based capillary glucose sample will be obtained. After this the participants will complete the second round of Loughborough Soccer Passing and Shooting Tests (LSPT) as subsequently described.

#### Loughborough Soccer Passing Test

The LSPT has been validated previously in several populations [21] and it has been established to reflect the physical exercise and game dexterity required to execute soccer practice. For example, it evaluates and scores the player’s capacity for executing short passes correctly with their feet. Previous trials [21] that applied this test have been able to differentiate professional players from those still in training in minor leagues, thus evidencing the yield obtained from the test that further allows us to evaluate the subject’s performance in this protocol.

The LSPT requires the participants to start with the ball (Pioneer Pro #5, CICADEX, San José, Costa Rica) next to their feet, standing next to the central cone. One evaluator will start timing the test using a hand-held stopwatch (Casio Handheld Stopwatch Timer Model HS-3 V-1R, Casio Computer Co., Ltd, Tokyo, Japan), from the moment the ball is touched forward moving out of the inner rectangle.

A second evaluator will be responsible for verbally identifying the color of the next target (i.e., meaning the zone towards where the patient needs to kick the ball). The specific target will be verbally identified just before the participant completed the previous pass. This will be repeated until the subject kicks the ball towards the four established zones, a total of 16 times. The same examiner will be used for each role to eliminate inter-rater variability. The order of passes will be determined by one of four randomly generated trial orders, so that each trial will consist of eight long (green and blue) and eight short (red and black) passing combinations.

The participants will be informed that the passes can only be executed from within the designated passing area, between the set of marked lines (see Fig. 2). They will also be instructed that upon retrieval from a previous pass, the ball must cross two of the inner marked lines before the next pass can be attempted. Furthermore, the players will be instructed that in order to attain the best performance in the LSPT they will have to execute the test as quickly as possible and make the fewest mistakes. The second evaluator will stop the clock when the last pass makes contact with the target area. The players will not know about the timing scores nor will they have any sort of performance feedback at any time during the data collection period.

